## Abstract

**Background:**

Despite the increasing use of pre- and posthydration protocols and low-osmolar instead of high-osmolar iodine-containing contrast media, the incidence of contrast-induced nephropathy (CIN) is still significant. There is evidence that contrast media cause ischemia-reperfusion injury of the medulla. Remote ischemic preconditioning (RIPC) is a non-invasive, safe, and low-cost method to reduce ischemia-reperfusion injury.

**Methods:**

The RIPCIN study is a multicenter, single-blinded, randomized controlled trial in which 76 patients at risk of CIN will receive standard hydration combined with RIPC or hydration with sham preconditioning. RIPC will be applied by four cycles of 5 min ischemia and 5 min reperfusion of the forearm by inflating a blood pressure cuff at 50 mmHg above the actual systolic pressure. The primary outcome measure will be the change in serum creatinine from baseline to 48 to 72 h after contrast administration.

**Discussion:**

A recent pilot study reported that RIPC reduced the incidence of CIN after coronary angioplasty. The unusual high incidence of CIN in this study is of concern and limits its generalizability. Therefore, we propose a randomized controlled trial to study whether RIPC reduces contrast-induced kidney injury in patients at risk for CIN according to the Dutch guidelines.

**Trial registration:**

Current Controlled Trials ISRCTN76496973

## Background

Iodine-containing contrast media are often used for diagnostic and therapeutic procedures and their use is the leading cause of hospital-acquired acute kidney injury [1]. Prospective studies demonstrate that contrast media are responsible for approximately 15% of acute kidney injury cases [2,3]. Despite the increasing use of pre- and posthydration protocols and low-osmolar instead of high-osmolar iodine-containing contrast media, the incidence of contrast-induced acute kidney injury is still significant [4,5]. This so called contrast-induced nephropathy (CIN) is defined as an absolute rise of ≥0.5 mg/dL and/or a relative increase of ≥25% in serum creatinine compared to baseline within 48 to 72 h after contrast administration without an alternative cause of kidney injury [6]. CIN is strongly associated with morbidity and mortality [7,8]. In patients with CIN, 8% need dialysis treatment and between 22% and 34% die during the index hospitalization [3,9-11]. In accordance with international guidelines, all patients who receive iodine-containing contrast are screened for risk factors of CIN, including measures of renal function (estimated glomerular filtration rate, based upon the MDRD formula) [12-15]. High-risk patients receive pre- and posthydration by saline solution infusion for 4 to 12 h. Furthermore, 48 to 72 h after contrast administration, serum creatinine should be measured [16]. Despite the identification of high-risk patients and the use of hydration protocols, the incidence of CIN still varies between 2% and 13% [17-20]. The exact mechanism underlying CIN remains to be elucidated. There is evidence to suggest that contrast media have direct toxic effects on the tubular cells resulting in altered mitochondrial function and apoptosis [21]. Moreover, ischemia-reperfusion injury of the medulla has been shown to play an important role [22]. The outer part of the medulla has an area with a high oxygen demand and is located at a distance from the vasa recta which supplies the medulla of blood. Contrast-induced vasoconstriction of the vasa recta induces ischemia-reperfusion injury of the medulla which contributes significantly to the pathophysiology of CIN. Remote ischemic preconditioning (RIPC) is a short and harmless discontinuation of blood supply to particular organs or tissue, followed by reperfusion [23,24]. A preconditioning stimulus is applied before the onset of prolonged ischemia. In animal models it has been found to reduce ischemia-reperfusion injury of the kidney [25]. Although the precise mechanism of RIPC remains unknown, two major pathways may play a pivotal role: the humoral and neurogenic pathways. Both are thought to induce various kinase cascades and eventually prevent opening of the mitochondrial permeability transition pore in the target organ, thereby reducing cell death [26]. A retrospective cohort study by Whittaker et al. indicated that multiple balloon inflations during coronary angioplasty (as a remote stimulus) might reduce CIN [27]. Furthermore, a recent pilot study by Er et al. showed that RIPC reduced CIN in high-risk patients undergoing elective coronary angiography [28]. However, there was an unusually high incidence of CIN (40%) in the control group. The question arises whether protection by RIPC, as an adjunct to standard preventive measures (that is, hydration and discontinuation of nephrotoxic drugs), also holds for patients with a lower risk of CIN. As generalizability of the results by Er et al. is confined to a selected group of patients with an unusual high risk of CIN, we propose a randomized controlled trial to study whether RIPC reduces contrast-induced kidney injury in patients at risk of CIN according to the Dutch guideline [14].

## Methods/Design

A multicenter, single-blinded, randomized controlled trial will be performed at the Radboud University Nijmegen Medical Centre and Slingeland Hospital Doetinchem. Inclusion will be performed by the physician researcher after written informed consent.

### Study population

A total of 76 patients will be randomized. Sealed envelopes are used to randomly assign consecutive patients in a 1:1 ratio to receive either sham preconditioning or RIPC (Figure 1). The study population consists of patients at risk of CIN according to criteria adopted from the Dutch guidelines: (1) eGFR <45 mL/min/1.73 m^2^; (2) eGFR <60 mL/min/1.73 m^2^; (3) eGFR <60 mL/min/1.73 m^2^ and two additional risk factors (that is, peripheral vascular disease, heart failure, >75 years of age, anemia, dehydration, use of diuretics and/or NSAIDs). Patients undergoing contrast procedures for diagnostic and/or treatment purposes are eligible. As patients receiving less than 100 mL of iodinated contrast media may not have an increased risk of contrast-induced kidney injury, an expected use of at least 100 mL was used as inclusion criterion [3,29].

**Figure 1 F1:**
[figure not shown]
**Study flow chart.** Legend: n.a.

### Inclusion criteria

1) Patients undergoing an interventional or diagnostic radiological procedure in which they receive an expected >100 mL intravascular contrast including:

••Thoracic and/or abdominal endovascular aortic repair

••Endovascular aortic repair

••Digital subtraction angiography

••Percutaneous transluminal angioplasty

••Percutaneous intentional extraluminal revascularization

••Carotic artery stenting

••Percutaneous coiling/embolization procedures

••Computed tomography

2) Patients who comply with the risk criteria for CIN according to the Dutch guidelines [14]

••Peripheral vascular disease, heart failure, >75 years, anemia (Ht < 0.39 men and <0.36 women, dehydration, diuretics and/or NSAID use)

3) Written informed consent.

### Exclusion criteria

•Age <18 years

•Hemodialysis or peritoneal dialysis

•Simultaneous participation in another interventional study

•Percutaneous coiling/embolization procedures of the kidney

•Impossibility to perform RIPC, due to pathology of both arms (for example, dystrophy, recent trauma, chronic wounds)

### Study protocol

All participating patients will receive the standard hydration schedule consisting of an infusion with saline 0.9% solution 3 to 4 mL/kg/h for 4 h prior to and 4 h after contrast administration. In patients with congestive heart failure or MDRD <30 mL/min/1.73 m^2^ a long schedule is used with an infusion of saline 0.9% solution 1 mL/kg/h for 12 h prior to and 12 h after the contrast administration. Nephrotoxic drugs (for example, metformin and diuretics) are discontinued at least 24 h before and after contrast administration [14]. Patients in the experimental group of the study will receive RIPC by four cycles of ischemia and reperfusion of the forearm by inflating a blood pressure cuff around the upper arm at 50 mmHg above the actual systolic pressure during 5 min followed by 5 min of reperfusion. In the control group, patients receive sham preconditioning by inflating the blood pressure cuff to 10 mmHg below the actual diastolic pressure during 5 min followed by 5 min of reperfusion (four cycles). The time between the last inflation cycle and the start of the intervention is planned within 45 min. In the interest of blinding, the investigator ensures that the inflation pressure is not visible for both the patient and the (interventional) radiologist. All patients receive Xenetrix 300 (0.6 to 0.85 Osmol/kg H_2_O), a low osmolar, non-ionic, and hydrophilic contrast medium [30,31]. Patients will complete a questionnaire to obtain all relevant baseline characteristics such as age, weight, previous contrast procedures, diabetes, vascular-related diseases, and (discontinuation of) medication. Chart review will be performed to complement and double check this information. Blood and urine samples are taken at baseline and 4 to 6 h after contrast administration. A final blood sample is taken 48 to 72 h after contrast administration. According to the Dutch guidelines, monitoring of renal function in high-risk patients is recommended within 48 to 72 h after contrast administration. All samples will be number coded before analysis to ensure blinding of the independent investigator performing the analyses.

### Primary endpoint

The primary endpoint is change in serum creatinine form baseline to serum creatinine within 48 to 72 h after contrast administration.

### Secondary endpoint

The secondary endpoints are the incidence of CIN (defined as an absolute rise of ≥0.5 mg/dL or a relative increase of ≥25% in serum creatinine over baseline within 48 to 72 h after contrast administration), rehospitalization, hemodialysis, and mortality within 6 weeks after contrast administration.

### Ethics, informed consent

An independent ethics committee, the Central Committee on Research involving Human Subjects, Arnhem-Nijmegen, approved the protocol. Oral and written informed consent from the patient will be obtained prior to inclusion.

### Adverse events

Although RIPC by repeated insufflations of a blood pressure cuff around the upper arm is considered safe, serious adverse events possibly related to the application of RIPC will be reported to the ethical committee. Mild adverse events are: transient discomfort due to compression and/or ischemia and the formation of ecchymosis (upper arm) or petechia (lower arm).

### Power analysis

In this randomized study, the change of serum creatinine from baseline to 48 to 72 h after contrast administration will be compared between the experimental and control group. Using serum creatinine change as continuous response variable increases the power of the study. In a previous retrospective cohort study at our center including 2,169 patients at risk for contrast-induced nephropathy, serum creatinine values decreased from 120 μmol/L at baseline to 118 μmol/L at 48 to 72 h after contrast administration due to adequate hydration protocols [17]. This mean change in serum creatinine (-2 μmol/L) was normally distributed with a standard deviation of 23 μmol/L. Based on existing evidence we assume that RIPC with hydration may provide a further decrease in mean serum creatinine from baseline to 48 to 72 h of approximately 14 μmol/L as compared to hydration only. This corresponds with approximately 60% of the effect that was found by Er et al. [28]. If the true difference in the experimental and control means is 14 μmol/L, we will need to study 34 experimental and 34 controls to be able to reject the null hypothesis with a power of 0.80 and an alpha of 0.05 calculated with a one-sided independent t-test. Based on existing animal [25] and human studies [32,33] investigating the influence of RIPC on renal ischemia-reperfusion injury, we assume that RIPC does not negatively affect renal function. Therefore, one-sided testing would be appropriate for this study. Expected lost to follow-up (for example, blood sampling not realized between 48 to 72 h) is approximately 5%. For this reason 38 patients will be included in both the experimental and control arm.

### Statistical analysis

The analysis will be performed on the basis of intention-to-treat principles. Student’s t-test will be used to compare normally distributed variables, and Mann-Whitney U test will be used to compare not-normally distributed continuous data. Categorical variables will be compared with the chi-square test. If univariable analysis reveals a significant difference in baseline characteristics, then a multivariable linear regression analysis will be used to assess its impact on the primary outcome measure (that is, change in serum creatinine between baseline and 48 to 72 h after contrast administration). A subgroup analysis will be performed to assess whether the impact of RIPC on the primary outcome measure is affected by the Mehran risk score. For this analysis patients will be divided into three equal groups (that is, tertiles) according to their Mehran risk score. Statistical analyses will be performed with SPSS 20.0. A probability value of <0.05 is considered to indicate statistical significance and 95% confidence intervals will be calculated.

The RIPCIN study is registered at: http://www.controlled-trials.com/ISRCTN76496973.

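### Whether creatinine change is analysed with adjustment, and for which covariates, depends on a baseline significance test and so on chance rather than prognostic value

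*Protocol article*

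**What the plan says.** The Statistical analysis section of the protocol article first lists the between-group tests: "Student’s t-test will be used to compare normally distributed variables, and Mann-Whitney U test will be used to compare not-normally distributed continuous data", with chi-square for categorical variables. It then gives the rule for adjustment: "If univariable analysis reveals a significant difference in baseline characteristics, then a multivariable linear regression analysis will be used to assess its impact". The outcome in question is creatinine change. The threshold comes at the end of the section: "A probability value of <0.05 is considered to indicate statistical significance and 95% confidence intervals will be calculated".

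The candidate variables are described in the Study protocol section as an open list: "all relevant baseline characteristics such as age, weight, previous contrast procedures, diabetes, vascular-related diseases, and (discontinuation of) medication". No covariate is named in advance for the primary outcome. The Mehran risk score appears only in a subgroup analysis by tertiles.

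The Power analysis section plans the main comparison as a one-sided independent t-test of creatinine change, with 34 evaluable patients per arm. On allocation, the Study population section says: "Sealed envelopes are used to randomly assign consecutive patients in a 1:1 ratio".

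**The concern.** With 1:1 randomisation and sound allocation, any baseline difference between arms is a chance event. A baseline p-value then says nothing about whether the variable matters for creatinine change, and that is the property that makes adjustment useful. The rule can fail in two ways:

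- It can bring in a variable that is unrelated to outcome because it happened to differ at p<0.05.
- It can leave out a strong predictor whose imbalance is sizeable but not significant in a trial of this size.

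What is at stake is the adjusted estimate. Whether one exists, and what it is adjusted for, would be settled by the draw of the randomisation. When one is produced, it stands beside the t-test result, and the article does not say which of the two carries the conclusion. The precision available from planned adjustment is also mostly lost.

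**Working it through.** **Inputs from the protocol article.** Target difference 14 μmol/L; SD of change 23 μmol/L ("was normally distributed with a standard deviation of 23 μmol/L"); one-sided alpha 0.05; power 0.80; 34 evaluable per arm (all from Power analysis). The significance threshold for the trigger is 0.05 (Statistical analysis).

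**Assumptions, not in the article.** The number of baseline tests k (5 to 20); independence of those tests; two-sided baseline testing; the correlation ρ between a covariate and creatinine change (0, 0.3, 0.5, 0.7).

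**Step 1: the plan's own figure.** n per arm = 2 × (1.645 + 0.842)² × 23² / 14² ≈ 33.4, so 34. The exact one-sided t-test needs 34.07 and has power 0.799 at 34. The stated sample size is reproduced without any adjustment.

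**Step 2: how often adjustment is triggered.** For one variable the chance is 0.05. In 40,000 simulated trials per scenario (34 per arm) the rate was 0.049 to 0.051 at every ρ, so prognostic value plays no part. For k independent variables the chance of at least one trigger is 1 − 0.95^k:

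| k | 5 | 6 | 8 | 10 | 15 | 20 |
|---|---|---|---|---|---|---|
| P(at least one) | 23% | 26% | 34% | 40% | 54% | 64% |

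The Study protocol section names six types of characteristic. The eligibility text adds others, such as eGFR, heart failure and anaemia, so about 10 is plausible but not documented.

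**Step 3: what a non-significant imbalance can do.** The largest imbalance that just misses p<0.05 at 34 per arm is t(0.975; 66 df) × √(2/34) = 0.48 SD. The expected shift in the unadjusted difference is ρ × 23 × 0.484:

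| ρ | shift (μmol/L) | share of 14 μmol/L |
|---|---|---|
| 0.3 | 3.3 | 24% |
| 0.5 | 5.6 | 40% |
| 0.7 | 7.8 | 56% |

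These are limiting cases at the edge of significance, not typical ones.

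**Step 4: power at 34 per arm, difference 14 (simulated, one covariate).**

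| ρ | unadjusted | triggered rule | pre-specified adjustment |
|---|---|---|---|
| 0.3 | 0.80 | 0.80 | 0.83 |
| 0.5 | 0.80 | 0.81 | 0.88 |
| 0.7 | 0.80 | 0.82 | 0.96 |

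The triggered column assumes that the adjusted result replaces the t-test when the trigger fires. In sample-size terms, 33.4 × (1 − ρ²) gives about 31, 26 and 18 per arm for power 0.80 with pre-specified adjustment.

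**Step 5: type I error (nominal 0.05, one covariate).** Pre-specified adjustment gives about 0.049. If the triggered result replaces the t-test, the rate is 0.047, 0.044 and 0.040 at ρ 0.3, 0.5 and 0.7. If success may be claimed on either result, it is 0.050 to 0.051. There is no material inflation.

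**The case against.** A reader might infer that the primary test itself becomes data-dependent and that its error rate suffers. The article does not support that. The Power analysis section plans a t-test, the sample size rests on it, and the regression enters to assess the effect of a baseline difference on the outcome. The most natural reading is a supplementary check, and nothing says that the regression replaces the t-test. Step 5 shows no material inflation on either reading, at least with one covariate.

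Four further objections have weight:

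- **Power.** The planned 0.80 is reached without adjustment, so the lost precision is a forgone gain, not a shortfall. Its size depends on ρ, which the article does not give. Nor does the article show that baseline creatinine or any other listed variable predicts creatinine change. At ρ = 0.3 the gain is small.
- **Trigger frequency.** The percentages rest on assumed k and independence. Age, diabetes, vascular disease and medication are likely to be correlated, which would generally lower them. They give the chance that an extra regression is run, not that a conclusion changes.
- **Baseline tests.** With sealed envelopes, a baseline test can flag faulty allocation. That is a use for the test, but not a reason to select covariates by it.
- **Condensed article.** The covariate list and the order of precedence may be in a fuller document. Their absence is not the finding.

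What remains is the trigger. The article states that rule itself, no other section corrects it, and even as a supplementary analysis it yields an adjusted result chosen by chance.

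**Conclusion.** The point holds for the adjusted analysis only. Under sound randomisation, the stated rule misses a strong predictor in about 95% of trials and adjusts for any given irrelevant variable in about 5%. At least one adjustment is triggered by chance in roughly a quarter of trials with 5 or 6 independent baseline tests, rising to 40% with 10 and 64% with 20. The rule captures almost none of the available precision: power 0.80 to 0.82, against 0.83 to 0.96 for planned adjustment over ρ from 0.3 to 0.7. All these ranges depend on k and ρ, which are assumed.

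The t-test, its type I error and its planned power are not called into question. This is a change worth making, not one on which the validity of the trial turns.

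**What to change.** In the Statistical analysis section:

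1. Delete the significance trigger.
2. Before the comparative data are analysed, name baseline serum creatinine as covariate, plus at most one or two other predictors that are already collected, such as centre. Fit that linear model for creatinine change whatever imbalance is observed.
3. State whether this model or the unadjusted t-test of the Power analysis section governs the conclusion. Either can be defended. Keeping the t-test as primary and the named-covariate model as supportive is the smaller change.
4. Present baseline characteristics descriptively, without using p-values to choose covariates.

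The cost is one to three degrees of freedom and a change of wording. No new data are needed, because the endpoint already requires baseline creatinine. The Trial status section reports 61 of the planned 76 patients included and the trial as ongoing, so the change can be made and dated before the comparative analysis.

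### Cutting the Mehran risk score into tertiles is a weak way to ask whether the RIPC effect depends on risk; a single interaction with the continuous score uses the same data better

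*Protocol article*

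**What the plan says.** The Statistical analysis section sets the question: "A subgroup analysis will be performed to assess whether the impact of RIPC on the primary outcome measure is affected by the Mehran risk score". It then fixes the grouping: "For this analysis patients will be divided into three equal groups (that is, tertiles) according to their Mehran risk score".

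The section does not say how the tertiles will be compared. The tests it lists are Student's t, Mann-Whitney and chi-square, judged at p<0.05 with 95% confidence intervals. Linear regression appears only as a follow-up to a significant baseline difference. The subgroup analysis is not described as exploratory.

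The size of the trial comes from two other sections. Under Study population: "A total of 76 patients will be randomized", in a 1:1 ratio, with no mention of stratifying by the score. Under Power analysis: "This mean change in serum creatinine (-2 μmol/L) was normally distributed with a standard deviation of 23 μmol/L", and "If the true difference in the experimental and control means is 14 μmol/L, we will need to study 34 experimental and 34 controls", "with a power of 0.80 and an alpha of 0.05 calculated with a one-sided independent t-test". Loss to follow-up is put at about 5%.

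**The concern.** The question is one of effect modification: does the RIPC-minus-sham difference change along a numeric score? Tertiles serve that question poorly in two ways.

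- **Information is thrown away.** Patients within a tertile are treated as having equal risk, and one gradient is replaced by two contrasts between small groups. In a trial sized only for its overall comparison, that loss is hard to afford.
- **The cut points belong to the sample.** They fall wherever these patients happen to lie, so another trial cannot reproduce the groups.

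There is also a risk that depends on how the tertiles are used. Three separate RIPC-versus-sham comparisons do not test whether the effects differ. Significance in one tertile and not in another is expected from noise alone at this size.

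The result will attract attention. The Background asks whether protection extends to patients at lower risk of CIN, and the Discussion uses the Mehran score to question the earlier pilot trial. An apparent dependence on risk, or an apparent lack of it, is likely to be quoted.

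**Working it through.** **1. Inputs from the protocol article.** SD 23 μmol/L, difference 14 μmol/L, one-sided alpha 0.05, power 0.80, 34 per arm needed, about 5% loss (Power analysis); 76 randomized 1:1 (Study population).

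**2. The plan's own figure.** The normal approximation gives n per arm = 2 × (1.645 + 0.842)² × 23² / 14² = 33.4, so 34. Exact noncentral-t power at 34 per arm is 79.9%. The stated 34 is reproduced.

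**3. Tertile size.** 76 × 0.95 ≈ 72 evaluable, and 72 / 3 / 2 = 12 per arm per tertile. This is an average: without stratification the arms within a tertile can be unequal, and tied scores can make the tertiles unequal.

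**4. Precision within a tertile.** SE of the RIPC-minus-sham difference = 23 × √(2/12) = 9.39 μmol/L. The 95% CI half-width is t(0.975, 22 df) × SE = 2.074 × 9.39 = 19.5 μmol/L, wider than the 14 μmol/L the trial is designed to detect.

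**5. Power to detect modification, tertiles against continuous score.** The gradients below are assumptions; the article gives none. Both tests are at 5% with 72 evaluable patients.

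- *Tertile interaction, F test with 2 and 66 df.* Noncentrality = sum of squared deviations of the three effects from their mean, divided by SE². For 0/14/28 this is (14² + 0 + 14²) / 9.39² = 4.45. For 7/14/21 it is (7² + 0 + 7²) / 9.39² = 1.11.
- *Continuous interaction, 1 df.* With a standard normal score, the outer tertile means lie at ±1.0908 SD. The slope per SD of score is 28 / (2 × 1.0908) = 12.8 μmol/L for 0/14/28 and 14 / (2 × 1.0908) = 6.4 for 7/14/21. Its SE is 2 × 23 / √72 = 5.42. The ratios are 2.37 and 1.18, with 68 df.

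| Assumed effect in low/middle/high tertile (μmol/L) | Tertile interaction, formula | Continuous interaction, formula |
|---|---|---|
| 0/14/28 | 44% | 65% |
| 7/14/21 | 14% | 21% |

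Simulating the linear gradient directly, with unequal arms within tertiles allowed, gives about 40% against 62% for the first row and about the same as the formula for the second. The ranges quoted are therefore 40–44% and 62–65%.

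**6. What would happen if the tertiles were tested one by one.** This is conditional, because the article does not state it. Take a true effect of 14 μmol/L in every tertile and 12 per arm. Let p be the noncentral-t power in one tertile.

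| | One-sided 0.05 | Two-sided 0.05 |
|---|---|---|
| Power in one tertile, p | 0.42 | 0.30 |
| All three significant, p³ | 7% | 3% |
| None significant, (1 − p)³ | 19% | 35% |
| Mixed, 1 − p³ − (1 − p)³ | 73% | 63% |

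Over 11 to 13 per arm the mixed share runs from 72% to 74% one-sided and from 60% to 65% two-sided.

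**The case against.** **The article does not say that tertiles will be tested separately.** A reader might infer from the list of two-group tests that RIPC will be compared with sham inside each tertile, and conclude that the plan will produce false signs of risk dependence in 63–73% of trials. The documents do not support that as a finding. The stated aim is worded as effect modification, which fits a treatment-by-tertile interaction. A statistical analysis plan that is not shown could specify that test, which would hold the false-signal rate at 5%. The objection stands, so the figures in step 6 are conditional only. It does not rescue the tertile cut, which the article does fix and which costs power under a proper interaction test.

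**Tertiles need no straight-line assumption, and the choice is made in advance.** Both are fair. A continuous interaction assumes that the effect changes linearly with the score, and the power advantage in step 5 was calculated under that assumption and a normal score. Naming one factor, one outcome and one grouping rule beforehand also limits searching for favourable cut points. Displaying tertile estimates beside the slope keeps a check on linearity.

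**The subgroup analysis does not decide the trial's main question.** Also fair. A reader might infer that the trial's rationale rests on the tertiles. The article addresses generalizability mainly by enrolling patients at risk under the Dutch guideline and giving them standard preventive measures, and the overall randomized comparison answers that. The tertile analysis is the only planned look at how the effect varies with risk, but the primary test does not depend on it.

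**The better method is still weak.** True: about 21% power for a 7/14/21 gradient. That supports an exploratory label; it is no argument for the less powerful option.

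**Conclusion.** The point holds as a matter of efficiency and presentation. The article commits to cutting a numeric score at sample-dependent points into groups of about 12 evaluable patients per arm in order to answer an effect-modification question. Compared with a continuous interaction, this lowers power from about 62–65% to 40–44% for a strong assumed gradient (0/14/28 μmol/L) and from about 21% to 14% for a modest one (7/14/21). These figures rest on 72 evaluable patients, the article's SD of 23 μmol/L, a normal score and a linear change in effect.

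Mixed significance across tertiles in 63–73% of trials under a uniform effect is a warning about one possible use of the tertiles, which the plan does not state. The change is worth making because it is cheap and uses data already being collected; the primary comparison is not in question.

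**What to change.** Replace the tertile analysis with one linear model of creatinine change on treatment, Mehran score as a continuous term, and their product. Report the interaction slope with its 95% CI and label the analysis exploratory. Show the RIPC-minus-sham estimate and 95% CI in each tertile for display only, without within-tertile p-values, so that readers can see departures from linearity.

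This is a separate model added for the subgroup question, since the primary comparison is a t-test and stays as it is. The cost is a sentence or two of analysis wording. No new data are needed, because forming tertiles already requires each patient's score. The article reports recruitment still under way, with 61 patients included, so the wording can be changed before analysis. The price is the linearity assumption, and power stays low for modest modification, which the report should say.
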